## Abstract

**Background:**

Evidence is emerging that women’s poor oral health and health practices during pregnancy are associated with poor oral health in their children and potentially an increased risk of pre-term or low-birth weight infants.

**Methods/Design:**

The Midwifery Initiated Oral Health-Dental Service (MIOH-DS) trial is a three arm multicentre randomised controlled trial which will recruit women from three metropolitan hospitals aimed at improving women’s oral health and service access and indirectly reducing perinatal morbidity. All three arms of the trial will deliver oral health promotion material, although a midwife oral assessment and referral to private/public/health fund dental services pathway (Intervention Group 1) and the midwife oral assessment and referral to local free public dental services pathway (Intervention Group 2) will be compared to the control group of oral health promotional material only. Midwives will undergo specific oral health education and competency testing to undertake this novel intervention.

**Discussion:**

This efficacy trial will promote a new partnership between midwives and dentists focused on enhancing the oral health of women and their infants. Should the intervention be found effective, this intervention, with existing on-line educational program for midwives, can be easily transferred into practice for large metropolitan health services within and beyond Australia. Further cost-benefit analysis is proposed to inform national health policy.

**Trial registration:**

Australian New Zealand Clinical Trials Registry ACTRN12612001271897.

## Background

Maintaining optimal oral health during pregnancy is now recognised as an important factor in the immediate and long-term health of women and children [1, 2]. Women are at a higher risk during pregnancy of poor oral health due to hormonal changes, dietary changes and increased nausea and vomiting [1, 3]. Poor maternal oral health has been linked to an increased risk of preterm birth and low birth weight infants [4, 5] particularly among women from lower socio-economic backgrounds [4]. Bacteria causing tooth decay can be transmitted following birth from the mother to the child though close physical contact, sharing of spoons and when mothers clean dummies with their mouths [6]. Fostering good oral health in women during pregnancy is seen as an ideal early intervention and good public health policy [7].

While some developed countries have implemented strategies to address the issue of maternal oral health during pregnancy, this has not been the case in Australia to-date [8, 9]. Only one-third of pregnant women consult a dentist when pregnant, even when oral health problems exist [9, 10]. This is partly due to the way oral health care is delivered in Australia with very limited access for low-income consumers to public dental services combined with the continuing high cost of private dental health care [11]. Even those eligible for public dental services will find themselves on lengthy waiting lists that are incompatible with the relatively short duration of pregnancy. This lack of access is also compounded by persistent, misunderstandings about the safety of dental treatment during pregnancy held by antenatal care providers, dentists and women [12].

There is mounting international evidence that midwives are the preferred health professionals to deliver the most effective maternity care for the majority of women worldwide [13–15]. As a result midwives are increasingly being supported to pass on key health messages to pregnant women, such as smoking cessation, weight control and drug and alcohol use [16]. In addition, midwives are often one of the first health professionals pregnant women encounter, and are therefore well-placed to identify and refer pregnant women early on in pregnancy when oral health problems are identified [17]. To assist midwives in delivering key messages and referrals an on-line oral health education program has been designed [18]. This education package developed and pilot-tested with midwives confirms their competence to undertake oral health care checks and provide oral health education to pregnant women [18, 19].

We now present a randomised controlled trial protocol to test the efficacy of a Midwifery Initiated Oral Health-Dental Service (MIOH-DS) in improving women’s oral health and service access and indirectly reducing infant morbidity.

### Aims and hypotheses

The aim of this study is to determine the effectiveness of the Midwifery Initiated Oral Health-Dental Service (MIOH-DS) in improving the uptake of dental services, oral health status, oral health knowledge, quality of oral health, and potentially influencing the incidence of low birth weight and preterm births in pregnant women compared to a midwife only intervention or a control group.

Pregnant women will be in one of 3 groups that will receive the following:Intervention group 1 (IG1) will receive the Midwifery Initiated Oral Health (MIOH) service involving the midwifery intervention (involving oral health education, oral assessment and referrals delivered by specifically trained midwives) and referral to existing dental services (public, private or health fund clinics).Intervention group 2 (IG2) will receive the MIOH-DS service which will include: a midwifery intervention (involving oral health education, oral assessment and referrals delivered by specifically trained midwives) and a dental intervention involving prompt treatment by trained dentists at specific public dental clinics.The control group (CG) will not receive any midwifery or dental intervention (current practice) beyond oral health promotional material but will be provided (if required) dental referrals after reaching the end point of this trial.

#### Primary hypothesis

We hypothesise that pregnant woman attending antenatal clinics receiving MIOH-DS (IG2) or MIOH (IG1) service will have a:

20% increase in the access/uptake of dental services30% improvement in their oral health and30% increase in their knowledge about maternal oral health; compared to the control group.

## Methods/Design

### Overall study design

The MIOH-DS study is being assessed using a three arm multicentre randomised controlled trial across three recruitment sites. Participants are randomly assigned to the intervention (two groups) or control groups with a goal of n=124 in each group at the time of post intervention follow up. There are two assessment periods: baseline (12–20 weeks gestation) and post assessment (28–42 weeks gestation). The study has been funded by the National Health and Medical Research Council of Australia for three years.

### Development of the intervention

The MIOH-DS intervention has been systematically developed and piloted using a developmental framework for complex interventions [20]. Through this process the evidence base was generated [8, 18, 21], the need for an intervention was identified [22, 23] and the feasibility assessed [22, 24]. The intervention involves midwives providing oral health education, assessment and referrals to pregnant women at their first antenatal visit. To undertake this role an online oral health training package for midwives was developed [18] and tested [19] and certified by the Australian College of Midwives as a continuing professional development (CPD) activity. The training package includes an oral health screening tool that was piloted [25] and evidence-based oral health promotional material for pregnant women endorsed by the state health department [26].

### Participants and recruitment

Participants are being recruited from antenatal clinics across three large metropolitan hospitals in Greater Western Sydney, Australia. Information about the study is provided to all pregnant women attending their first antenatal visit (booking visit). At all Australian antenatal clinics the first booking visit is attended by midwives. While waiting to see the midwife, pregnant women are invited to participate by an independent recruiter (dental assistant). Women are eligible for recruitment (inclusion criteria): if they are more than 18 years of age; do not have cardiac disease that would warrant the need of antibiotics for dental treatment; have not received dental treatment in the current pregnancy; have a single pregnancy of more than 12 and less than 20 weeks of gestational age; do not have any known foetal anomalies or other risk factors (including history of preterm birth) that would place the pregnancy at risk of complications; and are able to attend regularly for dental treatment if required. Informed written consent is obtained by the dental assistant from pregnant women who meet the study inclusion criteria.

A self-administered pre-questionnaire is then provided to obtain baseline demographic data, dental/medical aspects of the women’s health (such as uptake of dental services, quality of oral health) and pre-test oral health knowledge. In addition, the Oral Health Impact Profile-14 (OHIP-14) questionnaire will also be administered. The OHIP-14 is a subjective measure of oral health that has been used extensively and found to be a precise, valid and reliable instrument (α=0.88) [27, 28]. It contains 14 questions assessed on a 5-point Likert scale and the total scores range from 0–56 with higher scores indicating poorer oral health. The OHIP-14 assists in validation and determining the sensitivity and specificity of the midwifery oral assessment tool by representing the ‘gold standard’ for identifying participants at risk of having oral health problems. Participants from non-English speaking backgrounds are provided, if required, interpreter services and translated oral health promotional materials.

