#### Referrals

In this group, all pregnant women assessed to be at risk of poor oral health are referred to current dental services (either private, public or health fund) for treatment. The referral letter provided to pregnant women includes a covering letter and a survey/checklist—date of first visit, total number of visits required, treatment completed (item numbers), and dentists contact details—to be completed by the dentists and returned to the study investigators via fax. Information on the survey/checklist is also sought from private dentists whose contact details are provided by pregnant women in the post questionnaire. The checklist helps to assess the uptake of dental services, the common treatment requirements and associated dental costs, all of which are vital information to inform future economic evaluations and subsequent state and national policy in this area.

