##### Dental intervention

At the first appointment all the women undergo an initial dental oral assessment that includes medical history, followed by oral mucosal tissue examination, periodontal examination, dental caries examination and denture evaluation. A provisional diagnosis and treatment plan is made for those women having oral health problems. Once the consent for treatment is obtained, subsequent appointments are made in the second trimester to complete all the urgent treatment for women having dental problems. The second trimester (13–27 weeks) is considered a safe period to carry out necessary dental treatment^10^. The completion of treatment will take 1 to 3 additional visits depending on the treatment plan. Women having complex treatment needs such as root canal treatment are referred to the specialist for follow up care and are excluded from the study. After each examination participants are provided oral health education including oral hygiene instructions, brushing and flossing instructions and dietary counselling.

All women in the control group, intervention group 1 and group 2 (whether or not at risk of dental problems) undergo a final dental oral assessment by the study dentists at 28–38 week gestation period, the end point of this study. This examination is similar to the initial dental oral assessment and includes a detailed clinical examination. All women receive reminder cards from midwives followed up by telephone calls from the study administrative assistant to attend their final dental oral assessment. Pregnant women in the control group identified with a dental problem are referred to dental services after pregnancy. A post questionnaire having similar items to the pre questionnaire (demographic data, dental/medical aspects of the women’s health such as uptake of dental services, quality of oral health and post-test oral health knowledge), is administered to all women between 28–32 weeks. Contact details of private dentists who were consulted during pregnancy are also sought in the post questionnaire. The following methods are used to administer the post questionnaires: via the dental assistant/receptionist in the antenatal waiting room, via the midwife during the antenatal visit, over the phone when the final dental appointments are being made and via the study dentists at the final dental appointment.

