### Sample size

Sample size estimation is calculated on the outcome measure uptake of dental services using the assumption that 30% of pregnant women in the control group will access dental services during pregnancy (based on our survey [23] and existing Australian studies [10, 43, 44]. We expect the MIOH (IG1) and MIOH-DS service (IG2) will improve the uptake of dental services. The MIOH intervention is considered successful if at least 50% of the pregnant women in IG1 and IG2 will access dental services during pregnancy, a difference of 20% between the groups. To detect a difference of at least 20% between the groups with a two-sided test of proportions, alpha of 0.017 (three comparisons 0.05/3), and 80% power we determine using a statistical software that we require at least 124 patients in each group. Taking into account 10% attrition (refusal after randomisation-based on the results of our pilot survey) and 30 % loss at the endpoint (based on trials in this area - range 2-30%) [21] we will need to recruit 207 participants in each group.

Sample size was also calculated on the outcome measure oral health status using the assumption that 50% of pregnant women in the control group will have gingival bleeding (based on trials in this area) [21]. A 30% improvement in oral health status is expected in IG1 and IG2 (30% reduction in gingival bleeding). To detect a difference of at least 30% between the groups with a two-sided test of proportions, alpha of 0.017, and 80% power we determine using statistical software [45] that we require at least 52 patients in each group. Taking into account 10% attrition and 30 % loss at the endpoint we will need to recruit 87 participants in each group. Based on these estimations we will require a total of 621 participants for the trial (207 in each group). Interim analyses will be used to re-check the sample size after the first 100 women are recruited.

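### Uptake is worded as access during the whole pregnancy while eligibility excludes only earlier treatment, so a check-up before randomisation can count as uptake; count from randomisation instead

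*Protocol article*

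**What the plan says.** All references are to the protocol article.

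- **Eligibility** (Participants and recruitment). Women must "have not received dental treatment in the current pregnancy" and must "have a single pregnancy of more than 12 and less than 20 weeks of gestational age". Check-ups and consultations are not mentioned. The sections on Intervention group 2 and Dental intervention treat assessment and treatment as separate steps: assessment comes first, then consent to treatment, then further visits.
- **Outcome** (Sample size). The control assumption is that "30% of pregnant women in the control group will access dental services during pregnancy". Success means that "at least 50% of the pregnant women in IG1 and IG2 will access dental services during pregnancy", which is "a difference of 20% between the groups".
- **Baseline record** (Participants and recruitment). The pre-questionnaire covers "dental/medical aspects of the women’s health (such as uptake of dental services, quality of oral health"). The Randomisation section places allocation after baseline data collection.
- **Follow-up record** (Dental intervention). "A post questionnaire having similar items to the pre questionnaire" goes to all women at 28–32 weeks. It also asks for contact details of private dentists seen at any time in the pregnancy.
- **Dates** (Referrals). The checklist sent with the referral letter asks for "date of first visit, total number of visits required, treatment completed (item numbers"). The same information is sought from private dentists named in the post questionnaire.
- **Sources of uptake** (Outcome measures). These are the checklist, the study-clinic database, the post questionnaire, follow-up of referrals, and contact with private and health fund dentists.

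**The concern.** The entry criterion and the outcome describe different events. The criterion removes women already treated. The outcome counts any access, over a window that opens at conception and not at allocation. Entry at 12–20 weeks leaves three to five months in which a woman may have seen a dentist for a check-up only. On the wording she can be enrolled, and on the wording she has already met the outcome.

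A visit made before allocation is a baseline characteristic. Counted as an outcome, it is expected equally in every arm and carries no information about the intervention. It pulls the estimated difference towards zero. The affected outcome is the first listed in the primary hypothesis and the one that sets the sample size.

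**Working it through.** **1. The plan's own figure.** Inputs from Sample size: 30% v 50%, two-sided alpha 0.017, power 80%. With pooled variance under the null and no continuity correction,

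n = [z(1−α/2)·√(2p̄(1−p̄)) + z(0.80)·√(p₁(1−p₁)+p₂(1−p₂))]² / (p₂−p₁)²

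= [2.387·√0.48 + 0.842·√0.46]² / 0.04, which rounds up to 124 per group.

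Power at 124 is 80.1%. Inflation for 10% + 30% loss gives 124/0.60 = 207. Both stated figures reproduce exactly, so the arithmetic is not in question.

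**2. What counting earlier visits does.** Let q be the share of enrolled women, equal across arms in expectation, whose pre-randomisation check-up is counted. Let p be the rate among women with no earlier visit. The counted rate is q + (1−q)p, so the counted difference is (1−q) times the difference among women with no earlier visit. For this to equal the loss in the whole enrolled group, women with an earlier visit must respond to allocation as the others do. If allocation would not affect them at all, the overall difference is unchanged.

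**3. The size depends on what 30% and 50% mean.** The document gives no q, so it is an assumption here, shown from 2% to 10%.

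*Reading A: 30% and 50% are post-randomisation rates, with earlier visits added on top.*

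| q | Counted rates | Difference | Power at 124 | n for 80% | Recruited (n/0.60) |
|---|---|---|---|---|---|
| 2% | 31.4% v 51.0% | 19.6 points | 77.8% | 131 | 219 |
| 5% | 33.5% v 52.5% | 19.0 points | 74.1% | 141 | 235 |
| 10% | 37.0% v 55.0% | 18.0 points | 67.9% | 159 | 265 |

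*Reading B: 30% and 50% are whole-pregnancy rates that already contain q.* The planned comparison is then 30% v 50% as stated, and power stays at 80.1%. Among women with no earlier visit the rates are (0.30−q)/(1−q) and (0.50−q)/(1−q):

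- q=5%: 26.3% v 47.4%, power 83.9% with 124×0.95 ≈ 118 per group;
- q=10%: 22.2% v 44.4%, power 88.0% with 124×0.90 ≈ 112 per group.

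Reading B is the one that the Sample size section's wording supports, since both rates are expressed as access in pregnancy.

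**4. Can earlier visits be identified?** Largely, yes. Three of the listed sources (referral checklist, study-clinic database, follow-up of midwife referrals) arise from referral after allocation or from a service created for the study. An earlier visit would enter mainly through the post questionnaire and the dentists named in it. For those private dentists the date of first visit is sought, and the pre-questionnaire records uptake before allocation. Dating is thinnest for control women, who receive no referral letter during the trial, so it rests on the questionnaires and the dentists they name.

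**The case against.** The strongest reply has four parts.

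- **The article never says that earlier visits are counted.** A reader might infer that pre-randomisation check-ups do score as successes in every arm. The document does not support that. It neither counts nor removes them, and dental treatment may have been meant to cover any attendance. What stands is that the stated window includes such visits.
- **A condensed article may leave the counting rule to a fuller document.** This has force for the wording of individual questionnaire items, which are not shown. It has less force for the window, because the article does state one, the pregnancy, in both the success definition and the request for dentists' details.
- **The means of separating earlier visits already exist.** Baseline uptake is recorded before allocation and first-visit dates are sought. This is correct. It makes the remedy easy, but nothing states that these data will be used for that purpose.
- **No loss of power is established.** A reader might infer that the trial falls below its stated 80%. That requires Reading A, and the planning rates are worded as in Reading B. It would also be inconsistent to take 30% as a whole-pregnancy rate in order to guess q, and then as a post-randomisation rate to which q is added. This part stands in full.

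Any distortion is also expected to be the same in all arms and towards no effect, so it would not manufacture a benefit.

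**Conclusion.** The concern holds in a limited form. Eligibility is worded as treatment, uptake is worded as access across the whole pregnancy, and no rule starts the count at randomisation. Visits that allocation cannot cause can therefore enter the outcome in any arm.

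If a share q is counted, the difference shrinks by the factor (1−q), for example from 20 to 19 points at q=5%. This assumes that early attenders would otherwise respond like the rest. Because q is unknown, the effect may be small. The sample size of 124 per group (207 recruited) is arithmetically right, and its 80% power is not shown to be wrong. The lower figures (about 78% at q=2%, 74% at q=5%) apply only if 30% and 50% are read as post-randomisation rates. The point is a cheap improvement to the outcome definition and not a defect in the sample size.

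**What to change.** - In Outcome measures and Sample size, define uptake as at least one dental visit dated after randomisation. The final study assessment, which all arms are asked to attend, should stay outside the count.
- Date visits from the checklist, the study-clinic database and the private dentists contacted. Where an earlier visit is reported, ask for the first visit after the randomisation date.
- Word the post-questionnaire uptake item to ask about visits since joining the study. This matters most for control women, who have no checklist.
- Treat uptake reported in the pre-questionnaire as a baseline characteristic and not as an outcome event.
- In Participants and recruitment, state whether dental treatment covers check-ups. The criterion itself need not change.
- In Sample size, say whether 30% and 50% refer to the whole pregnancy or to the period after randomisation.

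**Cost.** A few sentences and one changed questionnaire phrase; most of the dates are already sought. Reported uptake will be slightly lower in all arms and no longer directly comparable with survey rates for the whole pregnancy. A whole-pregnancy figure can be reported descriptively if that comparison is wanted.
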